## Abstract

**Background:**

Generalised anxiety disorder (GAD) is a chronic and pervasive condition that generates high levels of psychological stress, and it is difficult to treat in the long term. Current pharmacotherapeutic options for GAD are in some cases only modestly effective, and may elicit undesirable side effects. Through targeted actions on the gamma-aminobutyric acid (GABA) pathway, the South Pacific medicinal plant kava (*Piper methysticum*) is a non-addictive, non-hypnotic anxiolytic with the potential to treat GAD. The evidence for the efficacy of kava for treating anxiety has been affirmed through clinical trials and meta-analyses. Recent research has also served to lessen safety concerns regarding the use of kava due to hepatotoxic risk, which is reflected in a recent German court overturning the previous kava ban in that country (which may in turn influence a reinstatement by the European Union). The aim of current research is to assess the efficacy of an ‘aqueous noble cultivar rootstock extract’ of kava in GAD in a larger longer term study. In addition, we plan to investigate the pharmacogenomic influence of GABA transporters on response, effects of kava on gene expression, and for the first time, the neurobiological correlates of treatment response via functional and metabolic imaging.

**Methods/Design:**

This clinical trial is funded by the Australian National Health and Medical Research Council (APP1063383) and co-funded by MediHerb (Integria Healthcare (Australia) Pty. Ltd). The study is a phase III, multi-site, two-arm, 18-week, randomised, double-blind, placebo-controlled study using an aqueous extract of noble kava cultivar (standardised to 240 mg of kavalactones per day) versus matching placebo in 210 currently anxious participants with diagnosed GAD who are non-medicated. The study takes place at two sites: the Centre for Human Psychopharmacology (Swinburne University of Technology), Hawthorn, Melbourne, Australia; and the Academic Discipline of Psychiatry (The University of Queensland) based at the Royal Brisbane and Women’s Hospital, Herston, Brisbane, Australia. Written informed consent will be obtained from each participant prior to commencement in the study. The primary outcome is the Structured Interview Guide for the Hamilton Anxiety Rating Scale (SIGH-A). The secondary outcomes involve a range of scales that assess affective disorder symptoms and quality of life outcomes, in addition to the study of mediating biomarkers of response (assessed via genomics and neuroimaging).

**Discussion:**

If this study demonstrates positive findings in support of the superiority of kava over placebo in the treatment of GAD, and also is shown to be safe, then this plant-medicine can be considered a ’first-line‘ therapy for GAD. Genomic and neuroimaging data may reveal clinical response patterns and provide more evidence of the neurobiological activity of the plant extract.

**Trial Registration Information:**

ClinicalTrials.gov: NCT02219880 Date: 13 August 2014:

## Background

Generalised anxiety disorder (GAD) is defined through cognitive and somatic symptomatology; involving primarily excessive chronic worry and anticipatory anxiety [1], in addition to a constellation of presentations such as sleep disturbances, restlessness, edginess/irritability, fatigue, concentration difficulties, and muscular tension [2]. GAD is ubiquitous and persistent, usually with early onset and high prevalence of co-morbid affective disorders and substance misuse [3–6]. Unfortunately, available pharmacotherapies have a modest clinical effect [7, 8] and may elicit undesirable side effects [9–11], and while psychotherapeutic treatments are found to be efficacious [12, 13], they are of limited utility for some patients [14, 15]. As a result, many GAD sufferers do not receive adequate treatment [16–18], thereby providing an impetus to explore other therapeutic options.

One such option is kava *(Piper methysticum)*, a plant native to the South Pacific, whose roots have been used in traditional medicine in the form of cold-water extractions (non-alcoholic) to treat a range of health conditions, including anxiety, stress, muscular spasms, pain, and menstrual disorders [19, 20]. The therapeutic effect of kava is based on the six major lipophilic kavalactones, of which kawain and dihydrokawain (see Fig. 1) have the strongest anxiolytic activity [21]. Limbic structures of the brain have previously been suggested as the principal site of kavalactone action [22]. Kavalactones exert their anxiolytic effect through an array of neurobiological activity, primarily from modulation of gamma-aminobutyric acid (GABA) receptors via blockade of voltage-gated sodium ion channels [23, 24], reduced excitatory neurotransmitter release via blockade of calcium ion channels [25, 26], and enhanced ligand binding to GABA type A receptors [27]. Other neurochemical effects include reversible inhibition of monoamine oxidase B [28], inhibition of cyclo-oxygenase [29], and reduced neuronal reuptake of dopamine [30] and prefrontal cortex noradrenalin [31]. This noradrenergic effect differentiates the central bio-behavioural effects of kava from those of alcohol and benzodiazepines [32], while the combination of GABA modulation and increased noradrenergic activation contributes to feelings of physical relaxation with increased hedonic tone, with no deleterious effects on cognition [33].

**Fig. 1 Fig1:**
[figure not shown]
Active constituents of kava

### Background evidence

A Cochrane review and meta-analysis of seven randomised clinical trials (RCTs) using kava mono-preparations (60–280 mg kavalactones) for the treatment of generalised anxiety symptoms found a significant reduction of anxiety on the Hamilton Anxiety Rating Scale (HAM-A) for kava compared with placebo (*P* = 0.01) [34]. Similarly, a more recent pooled analysis of six studies using kava versus placebo in the treatment of anxiety symptoms found a significant effect in favour of kava on the HAM-A, with an effect size (Cohen’s *d*) of 1.1 [35]. Our previous three-week double-blind, placebo-controlled, crossover RCT (*n* = 60), using a water-soluble rootstock extract of a noble kava cultivar in chronic generalised anxiety [36], involved a preparation standardised to a dose of 250 mg kavalactones. Following a placebo run-in phase there was a reduction of −9.9 points on the HAM-A in the first kava phase versus only a −0.8 point in the first placebo phase, and a reduction in the second crossover phase from kava of −10.3 points compared to a rise of +3.3 points for placebo (Cohen’s *d* = 2.24, *P* < 0.0001).

In a subsequent six-week parallel double-blind RCT [37] involving 75 participants with diagnosed GAD (58 randomised to 120 mg daily kavalactones titrated to 240 mg for non-response), a group × time interaction was found (*P* = 0.046) for a significant reduction in HAM-A scores in favour of kava over placebo. Further, kava significantly reduced participant anxiety by −4.2, representing a moderate effect size (Cohen’s *d* = 0.63). For participants with moderate-to-severe level anxiety (as assessed on the MINI Plus diagnostic interview), the treatment effect was more pronounced (*P* = 0.020), with a larger effect size (*d* = 0.80). The effects were still significant after controlling for baseline Montgomery–Åsberg Depression Rating Scale (MADRS) depression (*P* = 0.01), baseline Beck Anxiety Inventory (BAI) anxiety (*P* = 0.05), thyroid function (*P* = 0.02), and weekly caffeine use (*P* = 0.03). Further sub-analysis of participants with pure GAD and no other DSM-IV diagnosed co-morbid anxiety disorder (panic disorder, social phobia, post-traumatic stress disorder, obsessive-compulsive disorder) revealed a significant group × time interaction (*P* = 0.020; *d* = 1.28), with a reduction of −8.5 points for kava on the HAM-A compared to −2.3 points for placebo. As part of this trial we also examined five GABA transporter polymorphisms as potential pharmacogenetic markers of kava response. We observed a significant monotonic trend for two polymorphisms in which the number of rs2601126 T-alleles (*P* = 0.021) or of rs2697153 A-alleles (*P* = 0.046) was associated with significant reductions in HAM-A scores within the kava group.

## Trial objectives

The primary objective of this trial is to confirm the effectiveness and safety of kava as a pharmacological approach to treating GAD, by conducting a longer term, multicentre RCT with a large sample using a standardised pharmaceutical-grade aqueous rootstock extract of a noble kava cultivar in participants with current diagnosed GAD. As secondary objectives, we also seek to: 1) replicate our previously observed association between genetic variation in the GABA transporter and kava treatment response, 2) elucidate the mechanisms underpinning the efficacy of kava within the GABA and glutaminergic pathways through functional and metabolic neuroimaging, and 3) examine the effects of kava on the expression of selected genes within the GABA, glutamate, dopamine, serotonin, and adrenergic pathways.

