### Hypotheses

#### Primary hypothesis

Kava will be superior to placebo in the treatment of GAD symptoms, assessed by change in Structured Interview Guide for the Hamilton Anxiety Rating Scale (SIGH-A) [38] scores after the 16-week treatment phase.

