### Power analysis

The study will recruit a sample size of 210 participants (105 participants per arm). The study is powered to detect a small-to-moderate difference between active treatment and placebo on efficacy outcomes. Data will be analysed using data with at least one post-baseline, and all data including baseline measurement, in an intention-to-treat analysis. As such, a conservative effect size F of 0.15 on the primary outcome measure (SIGH-A) for a two-tailed analysis (with alpha = 0.05), and the study powered at 80 % (Z beta = 0.80), with a correlation among repeated measures (analysis of variance (ANOVA) model) over six time points, will require 206 participants (critical F of 3.88). A sample size of 206 (rounded up to 210) will be sufficiently powered to provide a statistical difference between active treatment and placebo groups (using the intention-to-treat analysis) with the data.

The sample size of the imaging component of this study is 40 per treatment arm (*n* = 80). Following 12-week supplement administration, a recent MRS study with a sample size of 24 (12 in each arm) detected significant changes in metabolites by 39 % [60]. Our sample size of 40 participants in each arm will provide higher statistical power compared to previous studies, whilst still maintaining sufficient power with a 10 % participant attrition rate, as well as attrition due to unreliable metabolite estimates in one or both time points.

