### Safety considerations

While kava is a Therapeutic Goods Association (TGA) listed, over-the-counter nutraceutical product in Australia and has not been shown to cause any confirmed serious adverse reactions in this country, concerns over hepatotoxicity have led to withdrawal or restriction in some other countries. As discussed in the literature [61–63], many reported cases have involved concomitant ingestion of other compounds with potential hepatotoxicity (such as other medications and/or alcohol). At the clinical level, a variety of case study data from patients with kava hepatotoxicity have been gathered, with probable causation reported in a few cases [63]. Previously reported hepatotoxicity issues identified with German kava products may also be due in part to the extraction (ethanol or acetone extraction) method; the use of non-water soluble chemical (ethanol or acetone) extraction techniques (the traditional solvent is water), and use of aerial parts of the plant and root and stem peelings, and poorly prepared, potentially contaminated raw material [63].

In response to safety concerns, the World Health Organization commissioned a report assessing the risk of kava products [64]. Recommendation 2.1.3 from the report suggested that products from water-based suspension preparations be preferentially used over acetonic and ethanolic extracts. The current study addresses these safety concerns by using standardised aqueous formulations of kava from the peeled rootstock of a noble cultivar (such cultivars are higher in kawain and dihydrokavain and lower in dihydromethysticin). Note that in June 2014, the German Federal Institute for Drugs and Medical Devices (Bundesinstitut für Arzneimittel und Medizinprodukte) overturned the previous 2002 ban on the use of kava products. As a European Union regulatory and guideline body, such a change has positive ramifications for the potential reinstatement of kava products based on ongoing empirical evidence from clinical trial research.

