### Monitoring and treatment compliance

Study staff involved in all aspects of participant recruitment, assessment, and monitoring hold postgraduate psychology qualifications, undergo training including inter-rater reliability of interviewer scale measures, and are supervised by psychiatrists and medical staff. This study has comprehensive medical supervision. Regardless, the occurrence of an adverse event (AE) may come to the attention of study personnel during study visits and interviews of a study subject presenting for medical care, or upon review of subject data by a study monitor. Any medical condition that is present at the time that the subject is screened for inclusion will not be reported as an AE. However, if it deteriorates at any time during the study, it will be recorded as an AE. All AEs will be graded for severity and relationship to study product. Participants will also be required to complete the Systematic Assessment for Treatment of Emergent Effects (SAFTEE) [65] at each assessment session to assess for AEs. All AEs will be recorded in the adverse event log in the participant case report form (CRF), including the seriousness, severity, and relationship to study product, duration, and outcome. In all cases, researchers will maintain contact with participants who experience an AE until it has been resolved and symptoms disappear. They will also be asked to notify their general practitioner. If a worsening of a participant’s mental state occurs, the study psychiatrist and/or clinical psychologist will be consulted and appropriate steps taken.

Liver function will be assessed pre-treatment, and participants with any abnormal results will be excluded as a safety precaution. In people with healthy liver function, it is not expected that any elevation of serum liver enzyme levels will occur (based on our previous studies using similar standardised pharmaceutical-grade extract of kava). Nevertheless, liver function will be closely monitored via blood samples at regular intervals throughout the study (weeks 2, 8, and 16).

Participants will be required to take the tablets as instructed during the 18 weeks of the study. At each assessment session they will be asked to return all unused tablets, which will be counted for compliance rate (tablet counts will be employed by an independent researcher).

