The anterior cingulate cortex’s (ACC’s) connectivity from lower limbic and hippocampal regions to the prefrontal cortical regions implies a central role in the organisation of affective and cognitive information. The ACC is thought to mediate affective and cognitive aspects of phenomena such as sadness recall, selective attention, loss, error and reward, suppression of negative emotion or cognitions, and autonomic processes that underpin anxiety states [71–79]. As such, (dysfunction within) the ACC may be a principal region underpinning GAD symptomatology, and is therefore the specific region under investigation for changes related to kava ingestion in the current study.

Some limitations to the study design are recognised. First, the design does not include a positive control product such as an SSRI, which may on some measures outperform the active treatment. Second, the use of imaging and genomic testing will need to ensure statistical correction applied for multiple comparisons, and thus the sample size must be reached to ensure adequate power in order to confirm any findings. Third, consideration of the external generalisability of study findings must be given, as the study sample will be ‘pure GAD’, that is, GAD that is currently untreated without co-morbid conditions such as major depression, and with no current symptom treatment regime, either pharmaceutical or psychotherapeutic.

In summary, if this traditional extract of kava is confirmed as safe and effective, it will provide a significant ‘Level 1’ treatment option which may help sufferers of anxiety and provide significant support to use in a clinical setting. It may also ease concerns about the potential reinstitution to restricted markets, which would provide socioeconomic benefit to poorer Pacific Island nations.

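### Confirming safety is part of the primary objective and underpins the first-line and market statements, but the trial is sized for efficacy alone and 105 people on kava for 16 weeks cannot exclude uncommon liver injury

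*Protocol article*

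**What the plan says.** **Objective and intended conclusions.** Under Trial objectives: "The primary objective of this trial is to confirm the effectiveness and safety of kava as a pharmacological approach to treating GAD". The abstract's Discussion says that if kava is superior to placebo "and also is shown to be safe, then this plant-medicine can be considered a" first-line therapy. The last paragraph of the main Discussion promises Level 1 status if the extract is confirmed as safe and effective, and adds: "It may also ease concerns about the potential reinstitution to restricted markets".

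**Hypothesis and sizing.** The primary hypothesis is efficacy only: "Kava will be superior to placebo in the treatment of GAD symptoms, assessed by change in Structured Interview Guide". None of the listed secondary hypotheses is a safety hypothesis, and the primary and secondary outcome lists contain no safety endpoint. The Power analysis section says "The study will recruit a sample size of 210 participants (105 participants per arm" and takes "a conservative effect size F of 0.15 on the primary outcome measure (SIGH-A) for a two-tailed analysis (with alpha = 0.05".

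**Where the article places the liver risk.** Under Safety considerations, "many reported cases have involved concomitant ingestion of other compounds with potential hepatotoxicity", with medicines and alcohol as examples. The same section also points to the product: solvent extraction, plant parts used and raw-material quality. It says that the chosen aqueous, peeled-rootstock, noble-cultivar extract addresses these.

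**Who is enrolled and what is collected.** Under Monitoring and treatment compliance: "Liver function will be assessed pre-treatment, and participants with any abnormal results will be excluded as a safety precaution". The exclusion criteria also remove current alcohol or substance use disorder, a named list of medicines, hepato-biliary disease and previous kava intolerance. Adverse events and a structured side-effect questionnaire are recorded throughout, with liver tests at weeks 2, 8 and 16.

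**The concern.** Confirming safety needs something to confirm it against: an endpoint, a margin, or a sample large enough to exclude a risk of stated size. The article supplies these elements for efficacy and none of them for safety. The safety question behind the market restrictions is hepatotoxicity, and the article describes it through case reports, with probable causation in only a few. A two-arm trial of this size says little about events of that kind.

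At stake is what the trial may conclude. If efficacy is positive and no liver injury is seen, a reader could take the safety condition as met and move on to the first-line and market statements. Those statements are not limited to the enrolled population or to 16 weeks. A separate analysis plan could add safety tables, but it could not repair this, because the objective, the sample size and the intended conclusion are all fixed in the article.

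**Working it through.** **1. The plan's own figure.** Inputs from Power analysis: f = 0.15, two-sided alpha 0.05, 80% power, m = 6 time points, 206 required, critical F 3.88. The correlation among repeated measures is not given; 0.5 is assumed.

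- Between-group repeated-measures F test: λ = f²·N·m / (1 + (m−1)ρ) = 0.0225 × 206 × 6 / (1 + 5 × 0.5) = 27.81 / 3.5 = 7.95, with 1 and 204 degrees of freedom.
- Critical F = 3.887 and power = 0.801, so 206 is reproduced. At ρ = 0.3 the requirement would be 148; at ρ = 0.7 it would be 264.

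The calculation contains SIGH-A quantities only. No safety rate or margin enters it.

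**2. What zero events would exclude.** Input: 105 people on kava (Power analysis) for 16 weeks (Treatment interventions, randomisation, and blinding).

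- One-sided 95% upper limit: 1 − 0.05^(1/105) = 2.81%, about 1 in 36.
- Upper limit of a two-sided 95% interval: 1 − 0.025^(1/105) = 3.45%.
- Dropout for the main trial is not stated. If 20% did not complete exposure (assumed), n = 84 and the limits are 3.50% and 4.30%.

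**3. Chance of seeing at least one event in 105 exposed,** 1 − (1 − p)^105. The article gives no event rate, so the values of p are illustrative.

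| True risk | At least one event | None seen |
|---|---|---|
| 1 in 100 | 65% | 35% |
| 1 in 500 | 19% | 81% |
| 1 in 1,000 | 10% | 90% |
| 1 in 10,000 | 1% | 99% |

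For a 95% chance of at least one event, n = ln(0.05)/ln(1 − p): 299 exposed at 1 in 100 and 2,995 at 1 in 1,000.

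**4. Comparison between arms for commoner events** (rates assumed; two-sided 0.05; normal approximation with pooled variance under the null). With 105 per arm, power is 22% for 2% against 5%, 40% for 1% against 5%, and 82% for 1% against 10%. Large differences in frequent events are detectable; modest ones mostly are not.

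**5. Eligibility set beside the Safety considerations section.**

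| Feature linked to liver cases | Handling in the trial |
|---|---|
| Alcohol | Use disorder excluded; drinking without use disorder not excluded |
| Other medicines | Named list excluded; unlisted medicines not generally barred; benzodiazepine or opioid analgesic use excluded only when more than two days per week |
| Extraction method, plant parts, raw material | Addressed by the choice of extract, not by excluding people |

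Separately, people with liver disease or abnormal baseline liver tests are not enrolled, and the article expects no enzyme rise in people with healthy liver function. The sample therefore omits part of the setting at issue, and a quiet liver profile is what the authors already expect.

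**The case against.** **The exclusions are proper.** Keeping out people with abnormal liver tests is a stated precaution. This stands in full: the exclusions are not a fault.

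**A reader might infer that the trial removes the very people in whom the article locates the liver risk.** The documents do not support that. Drinking short of use disorder, unlisted medicines and infrequent benzodiazepine or opioid use remain possible, and the article also places risk in product features that the chosen extract is meant to address. Only part of the setting is missing.

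**A reader might infer that a clean result is almost guaranteed.** That fails at 1 in 100, where the chance of at least one event is 65%. It is approached only at much lower risks, and the article's few probable cases have no denominator from which to derive a rate.

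**The conclusions are conditional and the limits partly acknowledged.** First-line use depends on safety being shown, the market statement is worded as a possibility, and no rule equates zero liver events with confirmed safety. The Discussion's third limitation notes restricted generalisability to untreated GAD without conditions such as major depression. This softens the point but does not remove it: the condition is that safety be shown or confirmed, which this design cannot deliver for uncommon liver injury, and the limitation is applied neither to liver safety nor to the event size that can be excluded.

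**Safety is wider than rare hepatotoxicity, and reporting detail belongs in the analysis plan.** Both are fair. Side effects and enzyme changes are collected under placebo control, and the Statistical analyses section already provides for 95% confidence intervals and Fisher's exact test. The absence of a safety table from the article is no finding.

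**Any trial of this size has this limit.** True, but not every trial of this size names confirmation of safety as a primary objective.

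**Conclusion.** The point holds as a mismatch between the safety claim and the design. Confirmation of safety sits in the primary objective, and first-line, Level 1 and market statements rest on it, while hypothesis, endpoint and sizing all concern efficacy. If no liver event occurs among 105 people exposed for 16 weeks, risks up to 2.8% (one-sided) or 3.5% (two-sided upper limit) are still not excluded, and an event at 1 in 1,000 goes unseen about nine times in ten.

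The bounds assume that all 105 are exposed and followed; dropout widens them. The 1 in 1,000 rate is an illustration, not an estimate from the article. The efficacy sample size, which reproduces under an assumed correlation of 0.5, is not in question here. The conclusion is not that kava is unsafe, nor that the eligibility rules are wrong. It is that a statement of confirmed safety about the hepatotoxicity question would go beyond the data.

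**What to change.** 1. In Trial objectives, make efficacy on the SIGH-A the sole confirmatory primary objective.
2. Restate safety as a descriptive objective: tolerability and liver tests over 16 weeks in adults who meet these eligibility rules.
3. Add to the limitations in the Discussion that uncommon liver injury cannot be excluded, with the upper bound of roughly 3% that applies if no event is seen, and that the enrolled group omits part of the setting linked to reported cases.
4. Limit the safety, first-line and market statements in the abstract and the closing Discussion to that population and length of exposure.

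How the limits are tabulated by arm can be left to the analysis plan. The cost is a less favourable claim. No patients or tests are added, and no clinical rule changes.
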